## Abstract

**Background:**

Although most older people living in nursing homes die there, there is a dearth of robust evaluations of interventions to improve their end-of-life care. Residents usually have multiple health problems making them heavily reliant on staff for their care, which can erode their sense of dignity. Dignity Therapy has been developed to help promote dignity and reduce distress. It comprises a recorded interview, which is transcribed, edited then returned to the patient, who can bequeath it to people of their choosing. Piloting has suggested that Dignity Therapy is beneficial to people dying of cancer and their families. The aims of this study are to assess the feasibility, acceptability and potential effectiveness of Dignity Therapy to reduce psychological and spiritual distress in older people reaching the end of life in care homes, and to pilot the methods for a Phase III RCT.

**Methods/design:**

A randomised controlled open-label trial. Sixty-four residents of care homes for older people are randomly allocated to one of two groups: (i) Intervention (Dignity Therapy offered in addition to any standard care), and (ii) Control group (standard care). Recipients of the "generativity" documents are asked their views on taking part in the study and the therapy. Both quantitative and qualitative outcomes are assessed in face-to-face interviews at baseline and at approximately one and eight weeks after the intervention (equivalent in the control group). The primary outcome is residents' sense of dignity (potential effectiveness) assessed by the Patient Dignity Inventory. Secondary outcomes for residents include depression, hopefulness and quality of life. In view of the relatively small sample size, quantitative analysis is mainly descriptive. The qualitative analysis uses the Framework method.

**Discussion:**

Dignity Therapy is brief, can be done at the bedside and could help both patients and their families. This detailed exploratory research shows if it is feasible to offer Dignity Therapy to residents of care homes, whether it is acceptable to them, their families and care home staff, if it is likely to be effective, and determine whether a Phase III RCT is desirable.

**Trial registration:**

Current Controlled Clinical Trials: ISRCTN37589515

## Background

Although most older people living in nursing homes die there, there is a dearth of good quality evaluations of interventions to improve their end of life care [1]. Residents usually have multiple health problems, making them heavily reliant on staff for their care, which can erode their sense of dignity. Maintaining dignity is given a high priority in health and social care strategy documents in most European countries, and particular concerns have been raised about loss of dignity in care [2]. Loss of dignity for people reaching the end of their lives is associated with high levels of psychological and spiritual distress and the loss of the will to live [3]. Pride, self-respect, quality of life, well-being, hope and self-esteem have been shown to be associated with dignity. For some people, a sense that nothing of one's life will be transcendent of death was associated with loss of dignity, and many felt that maintaining dignity was highly dependent on how they perceived themselves to be seen by others. [name]'s study also found that in-patients were more likely to suffer from loss of dignity.

An empirically-based model of dignity has been developed from interviews with hospice patients [4], which forms the basis of a brief psychotherapy to help promote dignity and reduce distress at the end of life [5]. The therapy addresses physical, psychosocial, existential and spiritual domains of concern or distress. It is brief, can be done at the bedside and aims to help both patients and their families. It comprises an interview with a trained therapist (usually a nurse or other health care professional), which is recorded, transcribed, edited then returned to the patient, who, when they are satisfied with it, can share or bequeath the resulting "generativity" document to people of their choosing. A preliminary evaluation of Dignity Therapy conducted with hospice patients in Canada produced positive findings for patients [5] and their families [6]. Randomised controlled trials of Dignity Therapy for hospice patients are underway in Canada, Australia and the USA, however, their findings may not be generalisable to those with a diagnosis other than cancer or the older people reaching the end of life in care homes.

An exploratory study of the views of older people in care homes on maintaining dignity supported many of the constructs in [name]'s dignity model, suggesting that Dignity Therapy has the potential to be of benefit to older people in care homes [7]. However, this is a very different context to that in which Dignity Therapy was developed, namely, specialist palliative care. This is likely to impact on the feasibility, acceptability and effectiveness of the intervention. One important difference to be considered is the high prevalence of cognitive problems in residents, the majority of whom are following a frailty rather than cancer illness trajectory. In-depth piloting which includes an exploration of the feasibility of delivering an intervention and attention to the context in which interventions take place, as planned here, is recommended in the new Medical Research guidance for developing and evaluating complex interventions [8]. As recommended in the MRC framework, we will also test our proposed outcome measures. The results will inform the design of a Phase III randomised controlled trial.

## Aims and objectives

The aims of the study are to assess the feasibility, acceptability and potential effectiveness of Dignity Therapy to reduce psychological and spiritual distress in older people in care homes. The specific objectives are to:

a) Determine whether Dignity Therapy is likely to increase peoples' sense of dignity or reduce psychological or spiritual distress.

b) Determine whether it is feasible to provide Dignity Therapy to older people in care homes.

c) Determine whether Dignity Therapy is acceptable to residents and their families.

d) Pilot methods for a larger (Phase III) randomized controlled trial (e.g. recruitment, randomization, follow-up, suitability of measures).

## Methods

### Study design

A Phase II open-label randomized controlled trial comprising two groups: (i) Intervention (Dignity Therapy offered in addition to standard psychological care), and (ii) Control group (standard psychological care). Consenting participants have been randomly allocated to one of these two groups after baseline (T1) measures have been collected. Standard psychological care will vary between care homes. None are providing Dignity Therapy. The nature of such care is being collected as part of this study.

### Randomization

Randomization was conducted by an independent statistician. Treatment allocation (Dignity Therapy or control) was performed by block randomization with a fixed block size of two. Allocation concealment is facilitated by using sequentially numbered opaque sealed envelopes for consecutive and eligible participants. To reduce the risk of bias, the research assistant opens the next envelope to ascertain which group the resident has been allocated to after baseline measures have been collected from participants.

### Ethical Approval

This study has been approved by The Joint South London and Maudsley and the Institute of Psychiatry NHS Research Ethics Committee (24/11/2008, ref: 08/H0807/75), and meets the requirements of the local Research Governance Framework.

### Participants

The sample will comprise 64 residents in care homes in South East London (Lambeth, Southwark & Lewisham). Based on our recent experiences of recruiting residents of care homes, we expect to recruit approximately 10 residents in each care home. Consequently we have opportunistically recruited six care homes to the study. These are local homes in which we have conducted research in the past which expressed an interest in Dignity Therapy. We will approach more care homes if this becomes necessary. Characteristics of care homes (size, ownership, registration, standard care) will be recorded and reported.

#### Inclusion criteria

Residents aged 65 years old or over are included. Not all residents have a "terminal" illness and they are not selected on the basis of receiving palliative care. However, all residents in nursing homes are frail and could be considered as reaching the end of life phase. Participants are not screened for spiritual or psychological distress, or loss of dignity, however, these are assessed at baseline to explore the potential moderating effects of these variables on the impact of the intervention.

#### Exclusion criteria

Residents are excluded if care home managers feel they are too ill to be interviewed, or unable to provide informed consent either due to cognitive problems, or to the severity of their illness, or because they are unable to understand English. Residents with moderate or severe cognitive impairment are excluded since their "generativity" documents are likely to reflect a fractured sense of self, which could be distressing to them and recipients of these documents.

Recipients of the Dignity Therapy documents (usually family or friends) are invited into the study to give their views on taking part in the study and the therapy.

### Sample size calculations

We are obtaining in-depth information on taking part in the study and receiving therapy from a relatively small sample, rather than aiming to detect significant group differences. One of the aims of the study is to estimate the effect size for an RCT. Allowing for a 25% loss at follow-up, a sample of 64 will give us 77% power to detect an effect size of 0.80 standard deviation units in the Dignity Inventory [9] between the intervention and control groups at the (two-tailed test) 5% level of significance. This will be sufficient to estimate recruitment, follow-up rates and the sample size for a Phase III trial, and to explore qualitative outcomes.

### Intervention group

The therapy is delivered by a palliative care nurse who has been trained in Dignity Therapy by [name] (who developed it). Training included the theoretical basis for the intervention, demonstrations of Dignity Therapy, a detailed overview of the manual, editing the Dignity Therapy documents and working with residents to produce a document that will be helpful for them and its recipients.

A standard framework of questions used in the therapy is given to residents in the intervention group (after randomisation) to give them the opportunity to think about their responses before the session (Table 1). The question framework provides a flexible guide for the nurse delivering the therapy (the therapist) to shape the interview, based on patients' level of interest and responses. The therapist follows the residents' cues, helping them to structure and organise their thoughts, for example, by asking questions about time sequences, how events are causally related to each other and facilitating the disclosure of thoughts, feelings and memories. These interviews are tape-recorded, quickly transcribed verbatim then shaped into a narrative using a formatted editing process. This includes clarifications (eliminating colloquialisms, non-starters and sections not related to the "generativity" material, such an interruptions), chronological corrections, tagging and editing any content that might inflict significant harm on recipients of the document (after discussion with the resident) and finding a suitable ending for the document which is appropriate to the residents' overall message. Another session is arranged for the therapist to read the edited transcript to the participants, who are invited to make any editorial suggestions, including identifying errors of omission or commission. Once these "generativity" documents are finalised, they are given to residents to share with anyone they choose. There is no evidence from previous studies that this has been problematic.

**Table 1 T1:** Framework of questions used in Dignity Therapy

• Tell me a little about your life history; particularly the parts that you either remember most, or think are the most important? Another way of putting this, which may elicit answers from some residents, is to ask, when did you feel most alive?
• Are their particular things that you would want your family to know about you, and are their particular things you would want them to remember?

• What are the most important roles you have played in your life (family roles, vocational roles, community service roles, etc)? Why were they so important to you, and what do you think you accomplished within those roles?

• What are your most important accomplishments, and what do you feel most proud of?

• Are there particular things that you feel still need to be said to your loved ones, or things that you would want to take the time to say once again?

• What are your hopes and dreams for your loved ones?

• What have you learned about life that you would want to pass along to others? What advise or words of guidance would you wish to pass along to your [son, daughter, husband, wife, parents, other(s)]?

• Are their words or perhaps even instructions you would like to offer your family, in order to provide them with comfort or solace?

• In creating this permanent record, are their other things that you would like included?

Since residents' conditions can fluctuate rapidly, the timing of the contacts can be relaxed and meetings rescheduled. If a resident's condition deteriorates, meetings are rescheduled up to three times before sensitively withdrawing them from the study. The therapist makes detailed notes of her experiences of giving each intervention and any deviations from the protocol. One in three therapy transcripts is randomly selected for review by the principal investigators. A quality assurance protocol has been developed to assess adherence to the Dignity Therapy protocol and deviations from the protocol will be reported as part of the feasibility study.

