### Control group

Residents in the control group have at least three interviews with the research assistant. Completing the measures and taking part in the interview gives them an opportunity to talk about their feelings. The extent to which they feel that this is therapeutic is explored in the interviews.

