### Outcome measures

Both quantitative and qualitative outcomes are assessed. These are collected from residents by face-to-face interviews at two time-points: approximately one (T2) and eight weeks (T3) after the dignity document has been completed, and the equivalent in the control group. Longer-term follow-up has not been included in the previous evaluation of Dignity Therapy, or in the current trials being conducted by [name] and colleagues. However, we believe it is important to evaluate the longer-term impact of the intervention. The feasibility of doing this is explored as part of this feasibility study. Quantitative measures have been validated and used with older people and are fairly quick and easy to use. Qualitative interview schedules have been developed for the study.

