#### Secondary outcomes for residents

*Potential effectiveness *is also assessed using: the Geriatric Depression Scale [11] (psychological distress); the Herth Hope Index [12] (hopefulness); the EQ-5D [13], and a two item measure used by [name] in the current trials of Dignity Therapy (quality of life). With the consent of participants, we are conducting a detailed qualitative analysis of the therapy transcripts to provide insight into concerns which might impact on the effectiveness of the intervention.

To assess *feasibility *of delivering Dignity Therapy in this setting, time taken to organize and conduct the Dignity Therapy sessions, transcribe and edit narratives, deviations from the therapy protocol and uncompleted interventions and the reasons, and the therapist's perceptions of competence as a result of training are recorded.

To assess the *acceptability *of Dignity Therapy we are conducting semi-structured interviews with residents in the intervention group to obtain their views on the intervention. The therapist is recording her experiences of delivering the therapy and her observations of resident's responses during and after the therapy. As suggested by Ferrell [14], we are reporting case studies of any difficult cases.

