### Analyses

#### Quantitative data

In view of the relatively small sample size, analyses will be mainly descriptive. However, between and within participant comparisons of outcomes will be conducted and the appropriate effect size estimates reported. The intervention and control group will be compared on the main outcome (a sense of dignity) and secondary outcomes (depression, hopefulness and quality of life). We will also compare Time 2 and Time 3 follow-up with baseline for both groups on these measures. The two groups will also be compared on demographic characteristics and baseline measures. If necessary these will be controlled for in the analyses. We will also report recruitment rates and compare drop-out rates and missing data in the two groups.

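### The rule for deteriorating residents withdraws them from the study rather than from therapy contacts, so T2 and T3 outcomes may be lost selectively from sicker residents in the intervention arm

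*Protocol article*

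**What the plan says.** The Intervention group section allows therapy contacts to be moved when a resident's condition fluctuates. On deterioration, "meetings are rescheduled up to three times before sensitively withdrawing them from the study". The sentences around it concern therapy delivery: the therapist's notes, transcript review and adherence checks.

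The Control group section has no matching rule. It says only that "Residents in the control group have at least three interviews with the research assistant".

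On sequence, Study design says "Consenting participants have been randomly allocated to one of these two groups after baseline (T1) measures have been collected". Intervention residents then have the therapy interview, after which "Another session is arranged for the therapist to read the edited transcript to the participants". Outcome measures places follow-up at "approximately one (T2) and eight weeks (T3) after the dignity document has been completed, and the equivalent in the control group".

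On losses, Sample size calculations uses one overall figure, "Allowing for a 25% loss at follow-up". Secondary outcomes for residents records "uncompleted interventions and the reasons" as feasibility data. Piloting methods for a Phase III trial records drop-out rates. Quantitative data plans to "compare drop-out rates and missing data in the two groups" and allows for control of demographic and baseline differences if needed.

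**The concern.** The rule ends participation, not only therapy, and no other section of the article says that T2 or T3 measures are still offered to a resident withdrawn this way. Three features make this a question of selection rather than ordinary attrition:

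- It acts after randomisation, so any loss falls on the randomised comparison.
- Its trigger is declining health, which is plausibly related to the primary outcome. The Patient Dignity Inventory covers physical and existential distress.
- It has more occasions to act in one arm, because intervention residents have extra meetings between randomisation and T2.

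The timing of follow-up adds to this. T2 and T3 are counted from completion of the dignity document, so a resident who never completes one has no stated date for either assessment.

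At stake are two quantities that the Sample size calculations section wants to pass on to Phase III: the effect size and the follow-up rate.

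**Working it through.** **1. The plan's own figure.** Inputs from Sample size calculations: 64 residents, 25% loss, 0.80 SD, two-sided 5%. Equal arms are implied by blocks of two.

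- Analysed: 64 × 0.75 = 48, or 24 per arm.
- Two-sample t-test power (noncentral t, 46 degrees of freedom, noncentrality 0.80 / √(2/24) = 2.77): 77.4%. The stated 77% reproduces.
- Standard error of the standardised difference: √(1/24 + 1/24) = 0.289 SD.

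Uneven loss at the same total costs little power: 20 and 28 analysed gives 76.3%. Extra loss in the intervention arm alone costs more: 20 and 24 gives 73.3%. Power is not the main issue.

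**2. Meetings after randomisation.**

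| | Intervention | Control |
|---|---|---|
| Therapy interview | 1 | 0 |
| Read-back session | at least 1 | 0 |
| T2, T3 | 2 | 2 |
| Total | at least 4 | 2 |

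This takes the reading least favourable to the concern, in which the rule covers research interviews in both arms.

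**3. Loss by arm (assumed).** The article gives no withdrawal rate. Assume a chance p per meeting, independent across meetings: loss = 1 − (1 − p)^k for k meetings.

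- p = 0.05: 1 − 0.95⁴ = 18.5% against 1 − 0.95² = 9.8%.
- p = 0.10: 1 − 0.90⁴ = 34.4% against 1 − 0.90² = 19.0%.

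With equal arms the p = 0.10 case averages (34.4 + 19.0)/2 = 26.7% overall, close to the planned 25%. A single overall loss figure can therefore look on target while the arms differ.

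**4. Spurious difference with no true effect (assumed).** Let the withdrawal score be 0.8 × illness + 0.6 × noise, and let illness correlate ρ with dignity distress. Removing the top fraction q of an arm lowers its mean distress by 0.8 × ρ × f(q), where f(q) = φ(z₁₋q)/(1 − q).

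- p = 0.05: f(0.185) − f(0.098) = 0.328 − 0.191 = 0.137. Shift: 0.8 × 0.3 × 0.137 = 0.033 SD to 0.8 × 0.5 × 0.137 = 0.055 SD.
- p = 0.10: f(0.344) − f(0.190) = 0.561 − 0.335 = 0.226. Shift: 0.8 × 0.3 × 0.226 = 0.054 SD to 0.8 × 0.5 × 0.226 = 0.090 SD.

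The range is 0.03–0.09 SD, or 0.033/0.289 = 11% to 0.090/0.289 = 31% of one standard error. If loss were strictly sickest first (loading 1 instead of 0.8), the range would be 0.137 × 0.3 = 0.04 to 0.226 × 0.5 = 0.11 SD.

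**The case against.** **Reach of the rule.** The sentence speaks of meetings, and the Recruitment Procedure section uses that word for the research assistant's visit. It can be read as a general rule for both arms. That stands as an ambiguity. It does not remove the imbalance, because the intervention arm still has the two additional meetings.

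**The model.** Deterioration follows calendar time more than number of meetings, and control assessments fall at the equivalent time. The therapy interview usually comes within days and transcription is quick, so the extra exposure is short. A resident too ill for sessions may also miss T2. All of this stands: the true difference in loss could be well below the figures above.

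**Adjustment.** Baseline dignity, comorbidity, performance status and activities of daily living are measured, and the analysis may control for them. This could shrink the bias. It cannot restore outcomes that were never collected, nor account for decline after baseline.

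**Purpose.** The study does not aim to detect group differences and its analysis is mainly descriptive. That limits the consequences, but estimating an effect size is a declared aim.

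**Stronger readings the article does not support.** A reader might infer that:

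- The sickest intervention residents will drop out more. This is an expectation from the structure; no figure in the article shows it.
- Collecting later outcomes is forbidden. No such prohibition appears; the article is silent, and the full protocol and Figure 1 are not available.
- Failure of therapy and loss to follow-up would be merged into one rate. The plan records uncompleted interventions with reasons and, separately, drop-out, which it compares by arm.
- Any bias must favour Dignity Therapy. That follows only if sicker residents report more distress, which is assumed here.

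**Conclusion.** The point holds as a fault of wording with consequences for the outcome data. Followed literally, the rule removes residents from the study after randomisation because their health is worsening, with more occasions to do so in the intervention arm and no statement that their outcomes are still sought.

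On the assumptions shown (5–10% withdrawal per meeting, correlation 0.3–0.5, illness as the main driver of withdrawal), the spurious difference is about 0.03–0.09 SD in favour of Dignity Therapy. Every one of those inputs is assumed. The shift is small beside the 0.80 SD in the power statement and the standard error of about 0.29 SD, so it would not by itself overturn the comparison. It is systematic, however, and would carry into the Phase III effect size. The follow-up rate is affected too, since part of the observed loss would come from the rule rather than from residents being unassessable. The stated 77% power is correct. Priority: should be fixed.

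**What to change.** Leave the rescheduling rule for sessions unchanged. Amend the text so that it distinguishes stopping therapy contacts from leaving outcome follow-up:

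- State whether the rule applies to the intervention arm only or to both arms.
- Residents in either arm who miss meetings stay in follow-up and are offered the T2 and T3 measures, at minimum the Patient Dignity Inventory, unless they die, cannot answer or decline.
- Where no dignity document is completed, schedule T2 and T3 at the equivalent time, as is already intended for control residents.
- Analyse these residents in the arm to which they were randomised.

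The cost is a change of protocol wording and a few more attempted visits to frail residents by the existing research assistant. Only part of the loss is recoverable, since some residents withdrawn after repeated rescheduling will be unable to answer.
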